### Data analysis

2.10

The primary outcome data will be analyzed using the intention-to-treat population, in which all patients will be maintained in their initial group assignment regardless of compliance and contamination, and missing data will be imputed using the last observation carried forward method. Meanwhile, we will also conduct a sensitivity analysis with the per-protocol population. The safety outcomes will be analyzed using a safety population including all participants who received treatment at least once. Mid-term and final data analyses will be performed at the end of week 52 and 104, respectively.

Normality will be detected using the Kolmogorov-Smirnov method. Normal continuous variables will be described using the mean and standard deviation and compared using a *t* test or analysis of variance. Non-normal continuous variables will be described using the median and interquartile range and analyzed with the Mann–Whitney *U* test. Categorical variables will be presented as the frequency and percentage and compared using Pearson *χ*^2^ test. The boundary of significance for the *P* value will be .05, which will be adjusted using the O’Brien & Fleming method for multiple comparisons.

According to our factorial design, we will explore whether there exists an interaction between HGMX and rabeprazole. If there are no significant interaction effects, we will compare the main effects of HGMX and rabeprazole. In addition, we will perform subgroup analysis stratified by type of PUD (GU vs. DU) and *H pylori* infection status (yes vs no). All statistical analyses will be conducted in Stata v14.0 software.

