#### Primary outcomes

2.5.1

1.The total effective rate of PUD treatment will be calculated as (clinical cure + markedly effective + effective)/total number of participants. Efficacy will be assessed by Sakita–Miwa's method.^[22]^ First, ulcer healing status will be classified into 6 categories:A1: the ulcer is round or elliptical, with a thick and white covering in the center; it can be accompanied by errhysis or blood clots and surrounded by obvious swelling, hyperemia, and oedema.A2: the ulcer is covered by yellow or white patches, with no bleeding and less swelling and edema.H1: the ulcer is healing; the coating of the ulcer becomes thin and subsides, hyperemia and edema disappear around the ulcer, and new capillaries appear.H2: the ulcer becomes shallow and small; the surrounding mucosa plica is central to the ulcer.S1: the white coating of the ulcer disappears, and the new ulcer mucosa is red.S2: the new ulcer mucosa changes from red to white.Then, the efficacy will be ranked according to the following 4 levels based on ulcer rehabilitation and recovery:Clinical cure: the ulcer completely heals with or without a scar.Markedly effective: the ulcer heals to grade H2 or improves 2 grades.Effective: the ulcer heals to grade H1 or improves by 1 grade.Noneffective: no efficacy by endoscopic observation.2.The quality of ulcer healing will be classified as follows by histopathological examination using Pan's criteria^[23]^:Good: integral villus and epithelium, many glands, good morphology, many capillaries, and limited inflammatory cell infiltration.Fair: short villus, incomplete or rough epithelium, fewer glands, structural distortion, few capillaries, and moderate inflammatory cell infiltration.Poor: few new epithelial cells, poor epithelium integrity, poor morphology of villus and glands, very few capillaries, and a large number of inflammatory cells.3.The changes in SQD symptoms will be assessed based on the Spleen Qi Deficiency Symptoms Grading and Quantifying Scale (SQD scale) score.^[19]^ This is a modified version of the classic scale that has a total of 15 items to assess 7 main symptoms and 8 secondary symptoms. Four aspects of SQD symptoms will be assessed, including severity, duration per episode, number of attacks per day, and number of affected days per week. The total score of each item is the sum of points for the 4 aspects in all items (items assessing the main symptoms receive double weight). The score ranges from 0 to 283 points, and a higher score indicates worse symptoms (see details in Supplementary file).

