### Discontinuation and withdrawal

2.7

Anyone who reports any of the following conditions during follow-up will be classified as withdrawal, and the patient will discontinue the trial.

1.Acute recurrent ulcer (eg, acute bleeding and perforation).2.SQD symptoms constantly worsen and require other interventions.3.Patient took <80% of the prescribed dose or any prohibited drug.4.Withdrawal owing to AEs.5.Patient request for withdrawal.

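### Last observation carried forward can count a patient withdrawn for ulcer relapse after week 12 as a treatment success at weeks 52 and 104

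*Protocol article*

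**What the plan says.** Section 2.10 (Data analysis) analyses the primary outcomes by intention to treat: "all patients will be maintained in their initial group assignment regardless of compliance and contamination". It then fixes the handling of gaps: "missing data will be imputed using the last observation carried forward method". The sensitivity analysis it names is per-protocol: "we will also conduct a sensitivity analysis with the per-protocol population". Analyses are planned at weeks 52 and 104.

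Section 2.7 (Discontinuation and withdrawal) states: "Anyone who reports any of the following conditions during follow-up will be classified as withdrawal, and the patient will discontinue the trial". Two of the five listed conditions are poor outcomes in themselves: "Acute recurrent ulcer (eg, acute bleeding and perforation" and "SQD symptoms constantly worsen and require other interventions". The others are low dosing or a prohibited drug, adverse events, and patient request.

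Section 2.5.1 defines the total effective rate as "clinical cure + markedly effective + effective)/total number of participants", graded by endoscopy. Healing to H1 or a gain of one grade is enough to count as effective. Section 2.6 schedules gastroscopy after baseline at weeks 12, 26, 52 and 104, and SQD symptoms at every follow-up visit (weeks 6, 12, 26, 52 and 104). Under section 2.4.4 all interventions have stopped by week 53.

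**The concern.** Treatment failure is itself a reason for missing data here, and the imputation rule ignores the reason. Consider a patient graded effective at week 12 who has an acute recurrent ulcer at week 20 and is withdrawn. Unless a further endoscopy is recorded, the last observation is the week-12 grade, and that grade is analysed as a success at weeks 52 and 104. Nothing in the document scores such a patient as noneffective.

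The Discussion says that the assessments after week 12 are meant to show the long-term effect of HGMX against placebo on the total effective rate, healing quality and SQD symptoms. Those are the three primary outcomes, so the later visits matter. At week 104 the rule can also carry a grade or score obtained during treatment into a year when all treatment has been stopped.

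At stake are the reported rates in each arm and, if withdrawal patterns differ by arm, the HGMX-placebo difference. The per-protocol analysis is no check on this. It changes who is analysed, not what is assumed about missing values.

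**Working it through.** The protocol states no figure for this effect, so there is none to reproduce. The sample size of 360 is not at issue.

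**Inputs from the protocol (section 2.9).** Maximum drop-out d = 15%; rates of 85% (HGMX) and 65% (placebo); 90 per group, hence 180 per pooled arm. 15% of 180 is 27 patients.

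**Assumed inputs (not in the document).** f = share of withdrawals that are failures, 25-75%. g = share of those failures whose last endoscopy was effective, 65-85%.

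**1. One arm, all withdrawals after week 12.** Upward bias = d × f × g.
- Low: 0.15 × 0.25 × 0.65 = 0.024, or 2.4 points.
- High: 0.15 × 0.75 × 0.85 = 0.096, or 9.6 points.

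**2. Difference between arms, true rate 65% in both, f = 75% in one arm and 25% in the other.**
- g = 0.65: 0.65 + 0.15 × 0.75 × 0.65 = 0.723, against 0.65 + 0.15 × 0.25 × 0.65 = 0.674. The false difference is 4.9 points.
- g = 0.85: 0.746 against 0.682. The false difference is 6.4 points.
- With 180 per arm and an unpooled two-sided 5% z test, these reject 17% and 27% of the time.

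**3. The same imbalance with true rates of 85% and 65%.**
- f = 25% on HGMX and 75% on placebo: 0.882 − 0.723 = 15.9 points (g = 0.85 and 0.65), or 0.882 − 0.746 = 13.6 points (g = 0.85 in both). The 20-point effect is understated.
- f reversed: 0.946 − 0.674 = 27.1 points, or 0.946 − 0.682 = 26.4 points. The effect is overstated.

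**4. Allowing for withdrawals before week 12.** Let k be the share of withdrawals before the first follow-up endoscopy, the same among failures and others. These patients have only the baseline endoscopy, so they show no improvement and count as noneffective. Assume 65% true success among withdrawals that are not failures, and g = 0.65 for anyone leaving after week 12. The analysed success rate among withdrawals is (1 − k) × 0.65 and the true rate is (1 − f) × 0.65. The bias is therefore 0.15 × 0.65 × (f − k).
- k = 0: this is step 1 with g = 0.65.
- k = f: the bias is zero.
- f = 25%, k = 50%: 0.15 × 0.65 × (−0.25) = −0.024. The rate is understated by 2.4 points.

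**5. Equal failure withdrawal with equal g.** Both rates are raised by the same amount and the difference is unaffected. If 15% of each arm is withdrawn for failure and g = 0.85, each rate rises by 0.15 × 0.85 = 12.75 points (about 23 of 180) and the bias in the difference is zero. If the failure withdrawals are 15% against 5%, the bias in the difference is 0.85 × (0.15 − 0.05) = 8.5 points, with its sign set by which arm has more.

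**SQD score.** No success is created here, because the outcome is a score. Carrying forward may keep an earlier, better score. How much worsening is lost depends on how much was already recorded at the last visit before withdrawal.

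**The case against.** A reader might infer that carrying forward inflates the total effective rate in both arms, or that it manufactures a benefit for HGMX. The document supports neither. Withdrawals before week 12 pull the rates down (step 4), and the bias in the difference depends on timing and reasons by arm, which are not given. If HGMX works and reduces relapse withdrawals, the rule works against it: step 3 gives 13.6 to 15.9 points instead of 20.

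It is also not certain that a relapse goes unseen. Section 2.5.2 defines recurrence, bleeding and perforation as measured by endoscopy, so an unscheduled endoscopy at relapse could become the last observation. The document neither requires nor excludes this. The point therefore holds only for patients who leave without one. Reporting recurrence as a secondary outcome does not correct the primary rate.

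The magnitudes deserve caution too. The 15% is a stated maximum, f and g are assumed, and three of the five withdrawal reasons are not failure criteria. The 26-27 point case is extreme: it needs 0.85/0.8875 = 96% success among HGMX patients who were not failure withdrawals, despite three times as many failure withdrawals as on placebo.

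For SQD, symptoms are assessed at every visit and the criterion is constant worsening, so some of it may already be in the carried score.

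Finally, a statistical analysis plan that is not shown may contain further sensitivity analyses, so their absence from the article is not a finding. What stands is that the article names the imputation method, and that method conflicts with its own withdrawal rules for failures after week 12.

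**Conclusion.** The point holds in a limited form. Sections 2.6, 2.7 and 2.10 together let a patient who relapses after a favourable week-12 or week-26 endoscopy, and leaves without another, count as a success at weeks 52 and 104. At week 104 they also let on-treatment values stand for off-treatment status.

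The net bias in each rate and in the HGMX-placebo difference is undetermined in size and sign. The 2.4 to 9.6 points per rate, and the 4.9 to 6.4 points in the difference under equal true rates of 65%, are illustrations. They rest on the maximum 15% drop-out, the assumed f and g, and no withdrawals before week 12. For the SQD score the effect is a possible retention of earlier, better values. The rule should be changed before the data are analysed, because the trial cannot know in advance which way it will err.

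**What to change.** Amend section 2.10 as follows.

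1. For the total effective rate, count patients withdrawn for acute recurrent ulcer, bleeding or perforation as noneffective at all later visits, over all randomised patients. This keeps the denominator of section 2.5.1.
2. For other missing endoscopic data, replace carrying forward with multiple imputation by randomised group, using for example earlier ulcer stage, ulcer type, *H pylori* status and SQD score. Handle withdrawals for SQD worsening here too: scoring them as noneffective would put a symptom outcome into an endoscopic endpoint. Analyse the SQD score with a mixed model for repeated measures or multiple imputation.
3. Do not carry on-treatment values past week 52.
4. Check robustness with a delta or tipping-point analysis by arm. Keep the per-protocol analysis as supplementary, since it does not test the imputation.

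The cost is revised wording and a little more programming, with no new patients or visits. The downside is that reported rates may be somewhat less favourable.

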### Site and participant recruitment

2.1

The participants will be enrolled from 11 hospitals in 3 cities in Jiangxi Province: the First Affiliated Hospital of Nanchang University, the Second Affiliated Hospital of Nanchang University, the Third Affiliated Hospital of Nanchang University, Jiangxi Hospital of Traditional Chinese Medicine, Nanchang Hongdu Hospital of Traditional Chinese Medicine, Nanchang Hospital of Integrated Traditional Chinese and Western Medicine, The Nanchang Third Hospital, Xinyu People's Hospital, Xinyu Hospital of Traditional Chinese Medicine, Jiujiang No.1 People's Hospital, and Jiujiang Hospital of Traditional Chinese Medicine. Trial enrolment will be advertised through oral promotion by researchers, hospital posters, and web page advertising. The recruitment was started at July 10, 2017 and is expected to be completed in July 2020.

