### Randomization and blinding

2.3

Patients who pass the eligibility assessment will be randomly and proportionally divided into four groups: Group A, B, C, and D. We generated a block randomization sequence using Microsoft Excel that was saved as enciphered data. For allocation concealment, we will adopt centralized random assignment. Independent researchers who do not participate in trial procedures other than the randomization process will recode the random sequence into continuous numbers and label the boxes of trial samples. Samples will be allocated sequentially to participants. In this way, no one will know the group into which the next participant will be assigned.

This trial will have 3 intervention periods: standard treatment period, maintenance treatment period, and recuperation treatment period. The standard treatment period will be open-label. During the maintenance and recuperation treatment period, the clinicians, patients, outcome assessors, and data collectors will be blinded in terms of the assignment of HGMX or placebo but the administration of rabeprazole will be open-label. Except in instances of a severe AE, all the participants, medical providers, data collectors, and outcome reviewers will strictly adhere to the blinded de∗sign until the trial has been completed. In addition, an independent committee will supervise the allocation concealment and blinding, and if blinding is violated, the corresponding patient will be excluded. Figure 1 gives an overview of the study design and procedures.

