### Sample size estimation

2.9

The main objective of this trial is to assess the effects of HGMX compared with placebo on the total effective rate. Therefore, the sample size estimation is based on the formula for a superiority design.^[24]^ Because there are no previous studies available for reference, we estimated a *P* of .85 (total effective rate in the two groups receiving HGMX) and a *P*_0_ of .65 (total effective rate in the 2 groups receiving placebo) according to the results of our pilot survey and expert opinions. In addition, we adopted a type I error (α) of 0.05, a type II error (β) of 0.2, and a maximum drop-out rate of 15%. Based on these assumptions and our funding constraints, we computed a sample size of 360, with 90 in each group.

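### Section 2.10 names only an unadjusted chi-square for the total effective rate; a prespecified covariate-adjusted analysis would be a cheap gain in precision, not the correction of an error

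*Protocol article*

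**What the plan says.** Section 2.9 (Sample size estimation) fixes the target: "The main objective of this trial is to assess the effects of HGMX compared with placebo on the total effective rate". The assumed success proportion under HGMX is given as one "of .85 (total effective rate in the two groups receiving HGMX"); for the pooled placebo arms the assumption is 65%. The error rates and dropout follow: "we adopted a type I error (α) of 0.05, a type II error (β) of 0.2, and a maximum drop-out rate of 15"%. The result is 360 patients, 90 in each of four groups.

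Section 2.10 (Data analysis) gives one comparison method for outcomes of this type: "Categorical variables will be presented as the frequency and percentage and compared using Pearson" chi-square. It names no covariate. Ulcer type and H pylori status appear once, as subgroup factors: "we will perform subgroup analysis stratified by type of PUD (GU vs. DU") and by infection status. Hospital does not appear in the analysis text. The section also plans an HGMX-by-rabeprazole interaction check followed by main effects, without naming a model.

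On design, section 2.1 states "The participants will be enrolled from 11 hospitals in 3 cities in Jiangxi Province", and section 2.3 states "We generated a block randomization sequence using Microsoft Excel that was saved as enciphered data". No stratification factor is mentioned.

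Section 2.6 has the outcomes measured at baseline. Ulcer type is known from the entry endoscopy, and H pylori status must be known to assign the week 1 to 2 treatment in section 2.4.1.

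**The concern.** Several baseline factors are plausibly prognostic on the article's own account.

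- **H pylori status.** It determines who receives two additional drugs in the first two weeks, and the Introduction links relapse to failed eradication.
- **Ulcer type.** Together with H pylori status, it is one of the only two subgroup factors.
- **Baseline Sakita-Miwa grade.** Part of the endpoint in section 2.5.1 is an improvement of one or two grades, so the starting grade enters the outcome by construction.
- **Hospital.** Clinicians at 11 hospitals carry out the examinations, and the endpoint is a descriptive visual grade.

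Outcome variation explained by these factors stays in the standard error of an unadjusted comparison. If they are strongly prognostic, the trial gives up some power and a narrower interval that it could have had from data in hand. The 20-point difference in section 2.9 rests on a pilot survey and expert opinion, so performance at a smaller effect is worth a look.

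**Working it through.** **1. The plan's own figure.** Inputs from section 2.9: 0.85 and 0.65, alpha 0.05, power 0.80, dropout 15%. Two-sided testing with zero margin is assumed, because neither is stated.

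n per arm = (1.960 + 0.842)² × 2 × 0.75 × 0.25 / 0.20² = 7.849 × 0.375 / 0.04 = 73.6, so 74. With dropout, 74 / 0.85 = 87.1, so 88. Four groups give 352, close to the stated 360 (88 vs 90 per group). The two-arm requirement was evidently applied to each of the four groups. The HGMX main effect pools two groups per side, so it has 180 vs 180.

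**2. Unadjusted power.** z = [d√n − 1.960 √(2p̄(1−p̄))] / √(p₁(1−p₁) + p₀(1−p₀)), with n patients per side.

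- 0.85 vs 0.65, n = 180: (2.683 − 1.200) / 0.596 = 2.489, power 99.4%. With n = 153 (180 × 0.85) it is 98.4%.
- 0.78 vs 0.65, n = 180: (1.744 − 1.251) / 0.632 = 0.780, power 78.2%. The 78% is an illustrative assumption; it is not in the article.

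**3. Adjusted power, by formula.** If covariates explain a share R² of outcome variance, adjustment acts like replacing n by n/(1 − R²). The article gives no R², so a range is shown.

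| Assumed R² | Equivalent total N | Power at 0.78 vs 0.65 |
|---|---|---|
| 0 | 360 | 78.2% |
| 0.02 | 367 | 79.1% |
| 0.05 | 379 | 80.3% |
| 0.10 | 400 | 82.4% |
| 0.20 | 450 | 86.6% |

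The largest gain is 86.6 − 78.2 = 8.4 points. At 0.85 vs 0.65, power stays between 99.4% and 99.9% over the same range, and the standard error of the difference falls from 0.0444 to between 0.0440 and 0.0397.

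**4. Simulation.** The formula does not charge for estimating the extra terms, so adjustment was also simulated: 4,000 runs per scenario, 11 hospitals, unstratified blocks of four, and a linear model with robust standard errors containing hospital indicators, ulcer type, H pylori status and rabeprazole. Hospital SD (logit scale) and factor odds ratios are assumptions.

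| Covariate strength | Hospital SD; ulcer type and H pylori OR; rabeprazole OR | Power at 0.78 vs 0.65, unadjusted → adjusted | Type I error, unadjusted / adjusted |
|---|---|---|---|
| Weak (R² about 0.03) | 0.3; 1.5; 1.0 | 78.1% → 77.9% | 4.6% / 4.9% |
| Moderate (about 0.09) | 0.5; 2; 1.5 | 78.2% → 80.0% | 5.3% / 5.4% |
| Strong (about 0.17) | 0.8; 2.5; 2.0 | 79.1% → 83.8% | 5.5% / 5.6% |

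At 0.85 vs 0.65 every scenario gave at least 99.3% both ways. With weak covariates, 11 hospital terms gain nothing.

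A smaller simulation (1,000 runs per scenario) used logistic regression with hospital indicators and added a baseline-grade indicator. It gave 79.6% → 81.4%, 78.1% → 84.5% and 79.8% → 85.9% at 0.78 vs 0.65, inside the same range. Both simulations used hospital indicators. Neither evaluated a random effect or grouped hospitals.

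**5. Sparseness.** At the planned rates there would be 180 × 0.15 + 180 × 0.35 = 27 + 63 = 90 non-responders, or 90/11 ≈ 8 per hospital on average and fewer in small ones. This is a reason not to fit 11 fixed hospital terms.

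**The case against.** The chi-square sentence is generic: it covers all categorical variables and does not call itself the primary model. The factorial paragraph implies some further method, since a single two-group Pearson test cannot yield an interaction, and its covariates could sit in a full protocol or analysis plan that is not shown. The unadjusted test is valid, and at the planned effect nothing is gained. The benefit appears only at an effect the article does not posit, under prognostic strengths it does not give.

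Most of this stands, and it limits the point. A reader might infer that the unadjusted test biases the result or inflates type I error. It does neither: simulated error is near 5%, and no stratified randomisation is described that the analysis would contradict. A reader might also infer that chance imbalance is left unhandled. Under randomisation the standard error and p-value already allow for it. It would likewise go too far to say that ulcer type and H pylori status are ignored, because both are planned subgroup factors, or that hospitals grade differently, because the article gives no such data and does describe defined grades, SOP training and a research associate for each centre. Finally, adjustment cannot be promised as equivalent to a fixed percentage of extra patients, because the weak-covariate case gives none.

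What survives is narrower. The article does state a method for this type of outcome, and a better one is available from data already collected. That is a proposal to replace a stated choice, not a complaint about missing detail.

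**Conclusion.** The point holds as a low-cost improvement in precision for the main HGMX comparison. The gain is negligible at 85% vs 65% with 180 vs 180. At 78% vs 65% it is roughly 0 to 8 power points on a base of about 78%. That range rests on an assumed smaller effect and on covariates explaining about 2% to 20% of outcome variance; the article supports neither figure. If the covariates turn out weak, the change does little harm provided hospital is handled sparingly.

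**What to change.** In section 2.10, or in the analysis plan before the week 52 analysis, specify for the total effective rate:

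- HGMX main effect (groups A+C vs B+D) from a logistic model adjusted for rabeprazole assignment, ulcer type, baseline H pylori status, baseline Sakita-Miwa grade and hospital.
- Hospital as a random effect, or with small hospitals grouped by a rule fixed in advance, not as 11 fixed terms.
- The result reported as a standardised risk difference with its 95% CI, the scale on which section 2.9 sizes the trial.
- The Pearson chi-square kept as a supportive analysis.

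The same model, with an added product term, can serve the interaction check that section 2.10 already plans.

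The cost is one or two sentences, with no new data and no extra patients. There are two small downsides. The adjusted odds ratio is conditional on the covariates, which is why the risk difference has to be standardised. And weak covariates or many sparse hospital terms would bring no gain. The covariates should be fixed before unblinding, so that their choice cannot look selective.

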Hou Gu Mi Xi (HGMX), a dietary TCM formula modified from Shen Ling Bai Zhu San, was developed in 2016. HGMX replaces Atractylodes (*Baizhu*), the only component in Shen Ling Bai Zhu San forbidden to use as food according to the regulations in China, with orange peel (*Jupi*) and is made into cornmeal with japonica rice and oats to improve patient compliance. As a result, HGMX is composed of 10 dietary herbs: ginseng (*Renshen*), tuckahoe (*Fuling*), coixenolide (*Yiyiren*), Chinese yam (*Shanyao*), lotus seed (*Lianzi*), Amomum (*Sharen*), Platycodon (*Jiegen*), white hyacinth bean (*Baibiandou*), liquorice (*Gancao*), and orange peel. In this formula, ginseng and tuckahoe play roles in invigorating qi and nourishing spleen; coixenolide, Chinese yam, lotus seed, and Amomum help improve the effects of ginseng and tuckahoe; and Platycodon, white hyacinth bean, liquorice and orange peel assist in promoting lung qi and regulating the waterway to improve the absorption of the herbs. The combination of these dietary herbs is expected to be efficacious at improving immunity and ulcer healing. In addition, HGMX should have a good safety profile because of its dietary property, and no adverse events (AEs) related to HGMX have been reported in the 3 years of post-market safety monitoring.

Therefore, we hypothesize that HGMX, in combination with routine treatments, will improve ulcer healing, increase the *H pylori* eradication rate, and reduce the recurrence rate in patients with PUD, with a good safety profile and good patient compliance. To verify this hypothesis, we plan to conduct a RCT in 11 tertiary hospitals.

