#### Extension period (weeks 53 to 104)

2.4.4

This is an observational period. All the interventions will be stopped, but follow-ups and outcome assessments will continue.

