
#### Secondary outcomes

2.5.2

1.Ulcer area (cm^2^) measured by endoscopy.2.Recurrence of PUD after standard and maintenance treatment, as measured by endoscopy.3.Incidence of bleeding and perforation after standard and maintenance treatment, as measured by endoscopy.4.*H pylori* eradication rate defined as a change in delta over baseline (DOB) value to <4 in the 13C-urea breath test during follow-up for *H pylori*-positive patients.5.Gastric function evidenced by analysis of gastrin-17 (pg/mL), pepsinogen I (ng/mL), and pepsinogen II (ng/mL).6.Changes in body weight (kilogram) and body mass index (kilogram per meter square).

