### Study visits

2.6

We will visit patients at baseline and at weeks 6, 12, 26, 52, and 104. In addition to the baseline measures of the outcomes, patients will undergo an eligibility assessment and provide demographic data, including gender, age, marital status, living situation, complications, medication history, and allergy history at baseline. During follow-up, we will examine ulcer histopathology at weeks 12 and 26; perform physical examinations, laboratory tests, and an electrocardiogram at weeks 12, 26, and 52; and examine *H pylori* infection and gastric function and perform gastroscopy at weeks 12, 26, 52, and 104. SQD symptoms, AEs, and concomitant treatments will be assessed or recorded at all follow-up visits. Table 2 gives an overview of the trial visits.

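### Under the only stated rule, recurrence to week 104 is a crude percentage tested by Pearson chi-square although withdrawal cuts follow-up short; a grouped-time analysis would suit it better

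*Protocol article*

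**What the plan says.** The Introduction makes recurrence part of the hypothesis: HGMX added to routine treatment is expected to "reduce the recurrence rate in patients with PUD". The Secondary outcomes list it as "Recurrence of PUD after standard and maintenance treatment, as measured by endoscopy", without a time point or denominator. Study visits plans to "perform gastroscopy at weeks 12, 26, 52, and 104", on the same schedule for every patient. The last of these falls in the extension period, of which the protocol says "All the interventions will be stopped, but follow-ups and outcome assessments will continue".

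Data analysis names a t test or analysis of variance, the Mann–Whitney test and, for outcomes of this type, the rule "Categorical variables will be presented as the frequency and percentage and compared using Pearson" chi-square. It names no life-table, time-to-event or person-time method. The intention-to-treat population and last observation carried forward are stated for primary outcome data.

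Under Discontinuation and withdrawal, anyone who meets a listed condition "will be classified as withdrawal, and the patient will discontinue the trial". The conditions include acute recurrent ulcer, worsening spleen qi deficiency symptoms that need other interventions, adverse events, the patient's own request, and "Patient took <80% of the prescribed dose or any prohibited drug".

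**The concern.** Recurrence accumulates over time and is detected only at scheduled endoscopies. A single percentage per arm is a fair summary when everyone is followed to the same point. Here a patient who leaves at week 20, for example, has no endoscopy after week 12, and a chi-square table has only two ways to treat that patient:

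- as recurrence-free to week 104, which nobody observed; or
- as absent, which discards the recurrence-free time that was observed while patients who recurred before leaving are kept.

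The first choice pushes the recurrence percentage down and the second pushes it up. Neither matters much for the comparison if withdrawal is balanced. If it is not, the test can show a difference where there is none, or mask one that exists. Some withdrawal reasons, such as amount of product taken, symptoms and prohibited drugs, could differ between arms. At stake is the long-term claim about recurrence, which the Discussion lists among the purposes of the assessments after week 12.

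**Working it through.** **Inputs from the protocol.** 360 patients, 90 per group, so 180 versus 180 for the HGMX main effect; maximum drop-out 15%; gastroscopy at weeks 12, 26, 52 and 104; significance level 0.05 (Sample size estimation, Study visits, Data analysis).

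**The plan's own figure.** None is given for recurrence. The sample size, set for the total effective rate (0.85 versus 0.65), is reproduced closely: 2 × 0.75 × 0.25 × (1.96 + 0.8416)² / 0.20² = 73.6, so 74 per group; 74 / 0.85 = 87.1, so 88 per group and 352 in total, against 90 and 360 stated. It does not depend on this point.

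**Assumptions, not in the protocol.** True recurrence by week 104 of 30% in both arms (20% and 40% also tried); everyone at risk from week 6; withdrawal unrelated to recurrence; withdrawal splits that average 15%.

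**Step 1, a limiting case by hand.** Let r be true recurrence and w the proportion withdrawn. If every withdrawal comes before any recurrence is seen and leavers count as recurrence-free, the crude rate is r(1 − w). With r = 0.30:
- w = 5%: 0.30 × 0.95 = 28.5%
- w = 25%: 0.30 × 0.75 = 22.5%

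The false gap is 6.0 points. Its standard error is √(0.255 × 0.745 × 2/180) = 0.0459, so z = 0.060/0.0459 = 1.31, and a two-sided 5% test rejects about 26% of the time. Simulation with withdrawal completed by week 26 gives 28.7% versus 22.8% and 24% rejection, which agrees.

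**Step 2, simulation with withdrawal spread over follow-up.** True recurrence is 30% in both arms and all randomised patients are in the denominator. Ranges come from different runs and withdrawal-time patterns.

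| Withdrawal by arm | Crude recurrence | Chi-square false rejection |
|---|---|---|
| 15% / 15% | 27.0% / 27.1% | about 5% (4.9% in 3,000 runs; 6.3% in a smaller set of 1,500) |
| 10% / 20% | 28.0% / 26.0% | 6.8% to 7.3% |
| 5% / 25% | 29.0% to 29.2% / 25.0% | 12.4% to 14.7% |

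Hand check of the 10%/20% row: √(0.27 × 0.73 × 2/180) = 0.0468; z = 0.020/0.0468 = 0.43; rejection about 7%. For 29.2% versus 25.0%: √(0.271 × 0.729 × 2/180) = 0.0469; z = 0.042/0.0469 = 0.90; rejection about 15%.

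**Step 3, the other denominator.** Keep only patients with a recurrence or a week-104 gastroscopy. At 5%/25% the rates become 30.5% versus 32.2%, so the arm with more withdrawals now looks slightly worse, with 6.0% rejection. At 15%/15% both rates are about 31.2%, above the true 30%.

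**Step 4, grouped-time methods.** In the 15%/15% and 5%/25% scenarios of Step 2, a life table recovers 30% in both arms. The log-rank test rejects 4.4% to 4.7% and a discrete-time complementary log-log model 5.4% to 5.5%.

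**Step 5, a real effect.** With true recurrence of 30% on placebo and 18% on HGMX, and withdrawal of 25% and 5% respectively, chi-square power is 43% over all randomised patients. It is 82% among those evaluable, inflated by bias. The discrete-time model gives 72.5%. With 15% withdrawal in each arm all three give about 71%.

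**The case against.** The case on the other side has real force.

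- **No test is assigned to recurrence by name.** The chi-square rule is generic, the article is condensed, and an analysis plan may exist. The missing denominator is therefore not a finding in itself. What stands is that the stated rule, applied as written, gives a crude percentage, and an analysis plan would have to depart from it.
- **Direction.** A reader might infer that the arm losing more patients will appear to relapse less. The documents do not support that. It requires unequal withdrawal, leavers counted as recurrence-free, and withdrawal largely unrelated to recurrence. With leavers dropped the sign reverses (Step 3), and acute recurrent ulcer is itself a withdrawal reason.
- **Size.** A 20-point gap in withdrawal is large. HGMX and placebo are blinded and dosed alike, and the Introduction reports no related adverse events after marketing. At a 5-point gap (12.5% versus 17.5%) false rejection is 4.9% to 5.8% for true recurrence of 10% to 40%.
- **Timing.** The endoscopy schedule is common to all and analyses are planned at weeks 52 and 104, so proportions at fixed visits are legitimate when follow-up is complete or losses are balanced.
- **The alternative is not assumption-free.** Censoring also assumes that withdrawal is uninformative, and the simulation built that in. Withdrawal for worsening symptoms may well break it. Nor can an ulcer that never healed recur: the sample size section itself expects 15% to 35% of patients not to reach even the effective grade.
- **Rank.** Recurrence is one of six secondary outcomes, and the total effective rate is the main objective.

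These points limit the size of the problem and shape the fix. They do not make the crude percentage the better method, since it cannot use partial follow-up and its answer depends on how leavers are classed.

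**Conclusion.** The point holds in a limited form. For a hypothesis-level outcome followed to week 104, the only stated rule gives a crude percentage and Pearson chi-square, while the protocol's own withdrawal rules make time at risk unequal between patients. Even with balanced 15% withdrawal the crude rate is off: about 27% or 31% for a true 30%, depending on the denominator. The comparison between arms is distorted only if withdrawal is unbalanced. False rejection is about 5% with no imbalance, 7% at 10%/20%, and 12% to 15% at 5%/25% with withdrawal spread to week 104. It is higher (24%) if the same withdrawals all occur by week 26.

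These figures rest on an assumed 30% recurrence, assumed withdrawal splits, withdrawal independent of recurrence, and everyone at risk from week 6. None of these comes from the protocol. No direction of bias can be claimed in advance. Sample size and the primary outcomes are unaffected. The change is worth making because a better method is available from data already planned.

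**What to change.** In section 2.10, name a method for recurrence:

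1. **Model.** A life-table or discrete-time model (complementary log-log link) over the scheduled gastroscopy intervals, with terms for interval, HGMX and rabeprazole. Censor at the last gastroscopy attended, and count withdrawal for acute recurrent ulcer as an event in its interval.
2. **At-risk set.** Patients with endoscopic healing, at risk from the gastroscopy that first shows it (week 12 at the earliest on the stated schedule). Because healing is itself affected by treatment, this set is selected after randomisation. Support it with an all-randomised analysis in which non-healing or recurrence counts as failure.
3. **Reporting.** Cumulative recurrence at weeks 52 and 104 with confidence intervals, and crude percentages as description only. Label any estimate for weeks 53 to 104 exploratory: it conditions on being recurrence-free at week 52 and rests on the single week-104 endoscopy.
4. **Sensitivity analysis.** Treat withdrawal for worsening symptoms as an event, since censoring it may be informative.

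The cost is some wording, one extra model and a result slightly harder to explain than two percentages. No visits, data or patients are added, the withdrawal rules stay as they are, and with balanced withdrawal power is unchanged at about 71% in the example above.
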